### Study design

A phase III, prospective, randomised, double-blinded, placebo-controlled study to investigate the effect of GnRHa as a protective agent during chemotherapy treatment. The study will include adult women and teenagers diagnosed with breast cancer, acute leukemias, lymphomas (Hodgkin and non-Hodgkin) or sarcomas (osteo, soft tissue and Ewing) treated with chemotherapy. The study will include approximately 300 subjects with breast cancer and up to 200 subjects with lymphoma, acute leukemias and sarcomas. After informed consent, baseline values will be collected and subjects will be randomised 1:1 to treatment with GnRHa (triptorelin) or placebo. Treatment will otherwise be according to best practice. The follow-up period starts at EoT and includes seven visits during the 5 year follow-up (figure 1).

**Figure 1 F1:**
[figure not shown]
Study time line. Baseline, screening/enrolment; R, randomisation, start of study treatment (−14 to +7 days from start of gonadotoxic treatment); EoT, 2–11 months after initiation of gonadotoxic treatment depending on disease-specific protocol; rs, research sample (including blood sample to measure ovarian markers), transvaginal ultrasound and QoL. EoT, end of treatment; QoL, quality of life.

### Setting, inclusion and study subjects

The study Sponsor is Karolinska University Hospital, Sweden and the study involves patient inclusion from 19 different sites around Sweden. Female subjects, aged 14–42 years at cancer diagnosis, with breast cancer or acute leukemias, lymphomas (Hodgkin and non-Hodgkin) or sarcomas (osteo, soft tissue and Ewing) as confirmed by histology and assigned for disease-specific chemotherapy will be included after signed informed consent. For study subjects under the age of 18, signed consent from both legal guardians are required in addition to consent from the study participant. Confirmed menarche, Eastern Cooperative Oncology Group (ECOG) performance status 0–1 and adequate bone marrow, renal, hepatic and cardiac functions and absence of other uncontrolled medical or psychiatric disorders are required for inclusion. Full inclusion and exclusion criteria are available in the prerecorded protocol (online supplemental material 1). The study opened for inclusion Q2 2023 and has a planned 3 year inclusion period. Primary endpoint data are estimated to be ready for analyses Q4 2027 and end of study, defined as the last study subject’s last follow-up visit, by Q4 2031.

### Randomisation

At the time of inclusion, inclusion and exclusion criteria are entered into a web-based randomisation application (ALEA) that will be operated by the Clinical Trials Office (CTO), Centre for Clinical Cancer Studies at Karolinska University Hospital. If all criteria are met, subjects are randomised to receive triptorelin or placebo in a 1:1 ratio using permuted block randomisation. Subjects will be stratified per diagnosis (breast cancer, lymphoma, sarcoma and leukaemia) and for subjects with breast cancer also for age groups (14–34; ≥35). The ALEA will assign a unique subject identification number and the randomisation arm to each subject. The subject’s identification number will be used on all study-related documents including the electronic Case Report Form (eCRF).

### Blinding

All personnel involved in the study, sponsor, investigators, site staffs and monitors, statisticians and subjects, except personnel preparing triptorelin/placebo at the local site and an unblinded monitor, will be blinded during the study. An unblinded research nurse at each site will prepare blinded triptorelin/placebo to subjects and manage registration in the web-based randomisation system ALEA, used to allocate blinded triptorelin/placebo to subjects at randomisation.

### Study treatment

The study treatment includes the addition of GnRHa (triptorelin (Pamorelin), intramuscular injection) or placebo (intramuscular injection) in addition to the best practice disease-specific cytostatic treatment. The first dose of triptorelin/placebo is given between −14 and +7 days from the start of the disease-specific gonadotoxic treatment as an intramuscular injection.

One triptorelin (Pamorelin) injection holds a dose that lasts either 1 month (3.75 mg) or 3 months (11.25 mg). The number of doses per subject will be adjusted to cover the disease-specific gonadotoxic treatment with as few injections as possible. Most study treatments correspond to GnRHa/placebo treatment for a duration of 3–6 months (1–2 injections). The amount of triptorelin/placebo is calculated based on the length of each block of disease-specific cytostatic treatment. The end of disease-specific gonadotoxic treatment is also EoT, and the first follow-up is planned 6 months after EoT (figure 1). Further information on the included chemotherapeutic treatment regimens is available in the full study protocol (online supplemental material 1).

### Study interventions

At the screening/baseline visit, the principal investigator at each site will ensure that each subject will be provided with written and oral information about the study. The informed consent form is signed before any study-related activities are carried out. A physical examination and complete medical history including demographic data will be performed before start of study treatment. Information regarding concomitant medications including ongoing fertility preservation measures, use of contraceptives and hormonal treatments will be collected at screening/baseline visit and changes in concomitant medications will be assessed throughout the study. Any reported changes will be recorded in the eCRF. Blood samples for measurement of routine blood parameters (a complete blood count, including B-hemoglobulin, white blood cells, differential count and platelets, liver status (alkaline phosphatase), alanine transaminase, aspartate aminotransferase, billirubin and gamma-glutamyl transferase), renal status (sodium, potassium, calcium, creatinine and albumin)) will be collected at baseline and EoT and research blood samples (hormonal markers: AMH, FSH, inhibin, estradiol and LH) and a transvaginal ultrasound (AFC and ovarian blood flow) will be offered at each study visit.

Reproductive outcome data, reproductive health, sexual health and quality of life will be collected through validated questionaires including EORTC QLQ C30, Hospital Anxiety and Depression Scale (HAD) and Female Sexual Function Index (FSFI) .

A full list of study procedures and interventions at each study visit is available in table 3 and in the full protocol (online supplemental material 1).

**Table 3 T3:** Study visits and study procedures

Procedure	Visit 1 Screening baseline	Visit 2 Day 0 (−14/±7 days) Initiation of study treatment (triptorelin/placebo)/ gonadotoxic treatment	Treatment visits during gonadotoxic treatment (triptorelin/placebo) (0–4 additional visits for study treatment) (±7 days)	Visit 3 EoT (±1 month) End of gonadotoxic treatment (1 or 3 months after last administration of triptorelin/placebo)	Visit 4 6 months (±1 months) From EoT	Visit 5–9 1,2,3,4,5 years (±1 months) From EoT
Inclusion/exclusion criteria	X	X				
Informed consent	X					
Fertility preservation	X					
Demography	X					
Physical examination	X					
Vital signs	X	X	X	X	X	X
Medical history	X					
Randomisation		X				
Safety blood samples*	X			X		
Pregnancy test (if older than 16 and sexually active)	X					
Biochemical markers†	X			X	X	X
Bone mineral density	X			X		X‡
Ultrasound§	X			X	X	X
Study treatment¶		X	X			
Questionnaire (baseline)	X					
Questionnaire (follow-up)				X	X	X
Concomitant medication	X	X	X	X	X	X
Adverse events (AE and SAE)		X	X	X	X	X

*Safety blood samples taken as clinical routine during the cancer treatment are recorded in the eCRF. Safety blood samples at baseline and EoT will be assessed as part of the study.

†Research samples including AMH, follicle stimulating hormone (FSH), inhibin, estradiol and LH.

‡Only at years 1 and 5 of follow-up.

§Antral follicle counts and ovarian Doppler flow.

¶Subjects randomised to treatment GnRHa will receive intramuscular injection(s) of triptorelin, 3.75 mg/month or 11.25 mg/3 months covering the duration of the gonadotoxic chemotherapy, subjects randomised to placebo will receive intramuscular injection(s) of placebo (NaCl 0.9%).

AE, adverse events; AMH, anti-Müllerian hormone; eCRF, electronic Case Report Form; EoT, end of treatment; GnRHa, gonadotropin-releasing hormone agonists ; LH, luteinising hormone; SAE, serious adverse events.

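### The only listed pregnancy test leaves out sexually active subjects aged 14–15 (and 16 on a strict reading), although they are eligible

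*Protocol article*

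**What the plan says.** Under Setting, inclusion and study subjects, the protocol article defines the population as "Female subjects, aged 14–42 years at cancer diagnosis" and requires "Confirmed menarche, Eastern Cooperative Oncology Group (ECOG) performance status 0–1". Every eligible subject, the youngest included, has therefore reached menarche. For the remaining criteria it refers to the supplement: "Full inclusion and exclusion criteria are available in the prerecorded protocol".

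Table 3, under Study interventions, has one pregnancy-test row: "Pregnancy test (if older than 16 and sexually active". It is marked at Visit 1 (screening/baseline) and at no other visit. The text before the table says "A full list of study procedures and interventions at each study visit is available in table 3 and in the full protocol".

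Other steps before dosing bear on pregnancy without testing for it. The article states "A physical examination and complete medical history including demographic data will be performed before start of study treatment", and says that "use of contraceptives and hormonal treatments will be collected at screening/baseline visit". Table 3 also marks the inclusion and exclusion check at both Visit 1 and Visit 2, and an ultrasound at Visit 1.

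**The concern.** The sexual-activity condition already picks out the subjects in whom pregnancy is possible. Among those subjects, the only effect of the added age condition is to remove the youngest from testing. The article gives no reason for the cut-off.

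Teenagers are not incidental to this trial. Their recruitment is listed among its strengths, leukaemia and sarcoma are included partly because they are common at that age, and ages 14–19 form a prespecified subgroup.

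What is at stake is individual safety. One triptorelin dose acts for 1 or 3 months (Study treatment), so it cannot be withdrawn if a pregnancy is found later. The schedule accepts the need for a test in older sexually active subjects but does not extend it to younger ones.

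**Working it through.** The plan states no figure on this point, so there is none to reproduce. The check compares the listed rules and then puts a range on the number affected.

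**Step 1: eligible ages against tested ages.**
- Eligible: ages 14 to 42, post-menarchal (Setting, inclusion and study subjects).
- Tested: older than 16 and sexually active (Table 3, Visit 1).
- Eligible whole-year ages not covered: 14 and 15 on either reading, and also 16 if the limit is taken as strictly above 16.
- The conditions are joined by *and*, so being sexually active does not bring a younger subject into the test.

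**Step 2: is there another listed test?**
- Baseline safety bloods: blood count, liver status and renal status; no hCG.
- Research samples: AMH, FSH, inhibin, estradiol and LH; no hCG.
- Visit 2, the treatment visits and follow-up: no pregnancy test marked.

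The article lists no other pregnancy test.

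**Step 3: how many subjects.** The document gives about 300 breast cancer subjects, up to 200 others, and 1:1 allocation. It gives neither the share aged 14–16 nor the share sexually active, so both are assumptions. I also assume that subjects this young come from the non-breast cohort.

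Subjects who lose a test = 200 × (share aged 14–16) × (share sexually active)

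| Assumed share aged 14–16 | Subjects | 10% active | 25% active | 50% active |
|---|---|---|---|---|
| 1% | 2 | 0.2 | 0.5 | 1 |
| 5% | 10 | 1 | 2.5 | 5 |
| 10% | 20 | 2 | 5 | 10 |

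- Range: 0.2 to 10 subjects.
- Share of the whole trial (300 + 200 = 500): 0.2/500 = 0.04% to 10/500 = 2%.
- On triptorelin, at 1:1: 0.1 to 5.

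The table counts ages 14–16, the strict reading. Under the same assumptions, ages 14–15 alone give no more than these numbers. They are tests not done, not pregnancies. The expected number of pregnancies is far smaller and cannot be estimated from the article.

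**The case against.** The strongest reply is that the article is a summary. The full criteria and the full procedure list are in a supplement that is not shown, and they may exclude pregnancy or require a test at every age. That limits what can be said about actual risk. It does not remove the point, because the cut-off is a printed rule and not an omitted detail. If the full protocol carries the same cut-off, the gap is real; if it tests at all ages, Table 3 misstates it.

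A second reply is that the trial injection adds little exposure. Subjects are enrolled as "assigned for disease-specific chemotherapy will be included after signed informed consent", and the first injection may come up to 7 days after chemotherapy starts. The decisive pregnancy check therefore belongs before chemotherapy, in routine care that a study schedule need not list. This stands as a reason to rate the point low. The study's own test is nonetheless placed at screening, and the age condition withholds it from the youngest.

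Third, other Visit 1 procedures might reveal a pregnancy, the ultrasound and hormone samples among them. They are only offered, the scan is transvaginal and listed for follicle count and blood flow, and research samples may be stored and not read at once. They do not replace a pregnancy test.

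Fourth, the size rests on two assumed shares and spans a 50-fold range (10/0.2). That is correct, and the range should be read only as showing that few subjects are involved.

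Finally, keeping the sexual-activity condition still relies on what a minor discloses, when both guardians must also consent. That is true too; the proposed change narrows the gap without closing it completely.

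**Conclusion.** The concern holds as a minor subject-safety point. On the article's own wording, sexually active subjects aged 14–15, and those aged 16 on a strict reading, have no listed study pregnancy test before the first injection. The textual conflict is certain; its practical effect is not, since routine care or the full protocol may already cover these subjects. Under the assumed shares, 0.2 to 10 of about 500 subjects are affected. Endpoints, randomisation, power and analysis are untouched.

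**What to change.** In Table 3, remove the age limit so that the pregnancy test applies to every sexually active subject regardless of age, and make the same change in the full protocol if it has the same cut-off.

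The cost is one table line, since the test is already a Visit 1 procedure. It adds 0.2 to 10 routine tests under the assumptions above, and never more than the assumed 2 to 20 subjects aged 14–16. No adult is tested additionally. The real burden is a sensitive conversation with young subjects, which sites should be ready to handle with care.

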### Study samples

The total volume of blood taken from each subject during the study is 200 mL; 40 mL (safety blood samples 2×20 mL) and 160 mL (research samples 8×20 mL) over a period from inclusion to 5 years from EoT. If analyses of study parameters are not immediate, research samples will be registered at Stockholms medicinska biobank at Karolinska University Hospital and handled according to the current biobank laws and regulations. The research samples will be coded/pseudonymised to protect the study subject’s identification. Biobanked research samples will be analysed at Karolinska Institutet or Karolinska University Hospital, Sweden.

### Outcome measures and endpoints

Levels of the primary variable, AMH in women with breast cancer, will be measured at baseline, at EoT and continuously during follow-up 6 months, 12 months and years 2, 3, 4, 5 after EoT to establish the primary endpoint of difference in AMH recovery at follow-up 12 months after EoT, relative to AMH levels at EoT, and the secondary endpoint of difference in AMH recovery at follow-up until 5 years after EoT, relative to AMH levels at EoT, as compared between the GnRHa group and the placebo group in women with breast cancer. The timing of the primary and secondary outcome analyses were based on longitudinal AMH measurements postchemotheraphy available from previous studies.^18 26^

Levels of the secondary variables, AMH in women with lymphomas, sarcomas and leukemias, FSH, inhibin and estradiol, AFC and ovarian blood flow, menstruation data and quality of life parameters will be measured at baseline, at EoT and continuously during follow-up 6, 12, months and years 2, 3, 4, 5 after EoT. Markers of bone mineral density will be measured at baseline and EoT, 1 and 5 years after EoT. A full list of secondary endpoints are in the study protocol (online supplemental material 1).

### End of study

The end of study is defined as the last study subject’s last follow-up visit. The principal investigator has the right to terminate the study for clinical or administrative reasons at any time. The study may be prematurely terminated due to a high number of serious adverse events (related or not related to the study medication) or if the enrolment process cannot be completed within a reasonable time frame.

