### Data analysis plan

An interim report will be produced after last enrolled subject has completed follow-up 12 months after EoT (primary endpoint). The interim report will include analyses of the primary and some secondary endpoints based on data assembled for each enrolled subject up until the time point corresponding to 12 months after EoT. The assembled data will be locked and the study unblinded only for the statisticians. Main analysis for the primary endpoint will be done using the ITT population. Analysis on the PP population will be performed as sensitivity analysis. Subgroup analysis will be performed on ITT population for AMH change on these prospectively defined subgroups:

Age (14–19; 20–34; **≥**35)Ovarian reserve (AMH) at baseline (0.68–2.3; 2.4–4.9; **≥**5 (µg/L)).Cancer diagnosis (breast cancer, lymphoma, sarcoma and leukaemia)Type of cancer treatment (high risk, intermediate risk and low risk).Exposure to gonadotoxic cytostatics (corresponding to cumulative dose, mg CPA)/.

Analyses results and aggregated descriptive summaries will be disclosed to the sponsor.

At the end of study, after the extended follow-up period of 5 years, and once all study data for the mentioned visits are collected and verified in the eCRF system, the unblinding of all subjects will take place for investigators and sponsor. All available data will be used in the statistical analysis. A subject who withdraws prior to the last planned visit in the study will be included in the analyses up to the time of discontinuation. All efficacy and safety analyses will be performed at end of study when the study database is released for unblinding.

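### The one specified safety ground for stopping cannot separate chemotherapy toxicity from triptorelin harm, and no by-arm safety analysis is placed before end of study, although the treatment-period adverse event data are complete by the 12-month lock

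*Protocol article*

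**What the plan says.** All locations are in the protocol article.

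- **End of study.** The specified safety ground is "The study may be prematurely terminated due to a high number of serious adverse events (related or not related to the study medication"). The sentence before it is broader: "The principal investigator has the right to terminate the study for clinical or administrative reasons at any time".
- **Blinding.** Those to be kept blind are listed as "All personnel involved in the study, sponsor, investigators, site staffs and monitors, statisticians and subjects". The exceptions are the local staff who prepare the injections and one unblinded monitor, and neither is given a safety-review role.
- **Data analysis plan, 12-month report.** "An interim report will be produced after last enrolled subject has completed follow-up 12 months after EoT (primary endpoint"). Its content: "The interim report will include analyses of the primary and some secondary endpoints". At that point, "The assembled data will be locked and the study unblinded only for the statisticians", and results and aggregated summaries go to the sponsor.
- **Data analysis plan, end of study.** "All efficacy and safety analyses will be performed at end of study when the study database is released for unblinding".
- **Safety and adverse events.** Events are registered from randomisation to 90 days after the last dose, with causality for each. Serious events reach the sponsor within 24 hours, suspected unexpected serious reactions go to EudraVigilance, and a safety update report goes to the regulator each year.
- **Study treatment.** Triptorelin or placebo is added to chemotherapy in both arms.

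**The concern.** Each statement is ordinary alone. Together they leave a gap. The named criterion counts serious events whatever their cause, in subjects who all receive cytotoxic treatment. Those who would act on it do not know the arms, so what they see is in effect a count over both arms. The comparison that could attribute an excess to triptorelin is placed last.

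The 12-month report makes the gap avoidable. The data are locked, the statisticians are unblinded and by-arm efficacy goes to the sponsor, but safety is not named in its scope. The trial gives an off-label drug against placebo to subjects from age 14. A benefit on AMH would be known for years without the matching comparison of harm.

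**Working it through.** **1. Timing, from the plan's own dates**

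- Setting, inclusion and study subjects: primary endpoint data in Q4 2027, end of study in Q4 2031. The gap is 5 − 1 = 4 years of follow-up after end of treatment (EoT), and the dates agree: 2031 − 2027 = 4.
- Both dates imply a last EoT of about Q4 2026. Inclusion from Q2 2023 for 3 years plus the longest treatment in Figure 1 (11 months) gives about Q2 2027 at the latest. A later last EoT moves both dates together, so the gap stays at 4 years.
- All dosing is therefore over before the 12-month report.

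**2. When the adverse event window closes**

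- One injection covers 1 or 3 months, and Table 3 puts EoT 1 or 3 months after the last one.
- Three-month injection: −3 months + 90 days ≈ EoT.
- One-month injection: −1 month + 90 days ≈ EoT + 2 months.
- The window therefore closes about 12 − 2 = 10 to 12 − 0 = 12 months before the 12-month visit. The ±1 month visit windows do not alter this.
- Table 3 also marks adverse events at every visit to year 5. If collection does continue, the 12-month tables are complete for the treatment period and interim for later events. Deaths accrue throughout follow-up in either case.

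**3. What a count over both arms can and cannot show (illustration)**

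The article gives no serious event rate and no threshold, so there is no plan figure to reproduce. The assumptions are:

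- 300 + 200 = 500 subjects, 250 per arm.
- Expected proportion with a serious event p = 10%, 20%, 30% or 40%.
- A count threshold c crossed by chance about 2% of the time, from P(X ≥ c) with X ~ Bin(500, p).

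Three scenarios, by expected change in the count:

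- (a) Chemotherapy events 5 points higher in both arms, no drug effect: 500 × 0.05 = +25.
- (b) Triptorelin adds 10 points in its arm only: 250 × 0.10 = +25.
- (c) As (b), with background 5 points below expectation: 25 − 25 = 0.

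By-arm power at two-sided 5%, n = 250 per arm, is Φ{(d − 1.96√[2p̄(1−p̄)/n]) / √[p₀(1−p₀)/n + p₁(1−p₁)/n]}. For 30% against 40%: (0.10 − 1.96 × 0.0427)/0.0424 = 0.386, so power is 0.65.

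| Expected p | c | Count crosses, (a) | Count crosses, (b) | Count crosses, (c) | By-arm power, (b) | By-arm power, (c) |
|---|---|---|---|---|---|---|
| 10% | 65 | 0.91 | 0.91 | 0.02 | 0.88 | 0.96 |
| 20% | 119 | 0.75 | 0.75 | 0.02 | 0.73 | 0.80 |
| 30% | 171 | 0.66 | 0.66 | 0.02 | 0.65 | 0.69 |
| 40% | 223 | 0.59 | 0.59 | 0.02 | 0.61 | 0.63 |

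The count reacts identically to (a) and (b), so it cannot say which occurred. A by-arm comparison rejects in (a) only at its 5% error rate. In (b) the count is about as likely to react as the by-arm test. It misses the harm in (c).

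**The case against.** Several stronger readings are tempting, and the document does not support them.

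- **That this is the only route to stopping for safety.** It is the only specified one. The principal investigator may also terminate for clinical reasons at any time.
- **That triptorelin harm cannot be seen.** Causality recording, 24-hour reporting, unexpected-reaction assessment and the annual report all operate while subjects are dosed. A count also rises with drug harm, as scenario (b) shows. The weakness is attribution.
- **That the text prescribes a pooled count.** That is an inference from the wording on relatedness together with blinding.
- **That recruiting more leukaemia or sarcoma subjects could stop a harmless trial.** This needs a reader who ignores diagnosis, and nothing says so. The termination sentence is permissive.
- **That there is no independent review of events by arm.** The article summarises a full protocol that is not shown. Such arrangements may be there, and their absence here is no finding.

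It can also be said that the 12-month scope does not exclude safety. The secondary endpoints chosen for it are not listed, the secondary objectives include comorbidities, bone density, recurrence and survival, and a safety analysis set is defined. The end-of-study sentence covers efficacy too and is plainly not literal there. That is fair, but the 12-month report explicitly qualifies the efficacy half, and nothing qualifies the safety half.

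Replacing the count with an arm-imbalance criterion would be a debatable trade. It would drop the named ground for stopping when events are high in both arms, and it would need an unblinded reviewer whom the article does not identify.

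**Conclusion.** The point holds in two parts. First, the specified safety ground cannot by itself distinguish chemotherapy toxicity from triptorelin harm. This follows from the text without any assumed rate. The probabilities above only illustrate it and depend on assumed rates of 10% to 40%.

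Second, as written, by-arm safety analysis waits for end of study, about 4 years after by-arm efficacy is available to the sponsor. The 90-day adverse event window will by then have been closed for about 5 years (4 years 10 months to 5 years after EoT). This rests on the 90-day rule in the Safety section. If the Table 3 schedule governs instead, it still holds for treatment-period events.

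Neither part affects the validity of the primary AMH comparison. The second is a cheap improvement that should be made. The first calls for clarification, not for a new rule.

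**What to change.** 1. **Data analysis plan.** State that the 12-month report includes adverse event, serious adverse event and death tables by randomised arm and diagnosis stratum, and limit the end-of-study sentence to the final analyses. The efficacy result is then not disclosed without the matching safety comparison. The cost is a little programming, since the data are locked and the statisticians unblinded at that point. One care is needed: sparse strata should be shown in aggregate, because the sponsor stays blinded to individual allocation. This comes after dosing has ended, so it brings the safety comparison forward but does not protect subjects during treatment.
2. **Blinding, End of study, Data analysis plan, Safety and adverse events.** Reconcile these on what the serious event criterion compares, who sees events by arm, and when. If the full protocol already settles this, a cross-reference is enough. Align the 90-day window with Table 3 in the same edit. This costs about a paragraph. No stopping rule or threshold is proposed.
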